## Discussion

Recent years have witnessed a marked awareness of the many adverse health consequences of high intake of free sugars, especially in the form of SSBs [18–27, 42, 43]. Curbing SSB consumption, which has increased rapidly around the world in the last decades [13], has accordingly become a public health priority [11, 33], with recent research focusing on identifying effective interventions.

A number of interventions aiming to reduce SSB consumption exist and have been assessed in recent studies. These include the use of education [44] and the provision of caloric information through labelling [45–47]. However, the effects of these have been, at best, modest with the latter being observed in one study to increase, rather than decrease, consumption [47]. To achieve significant reductions in SSB consumption, it has been argued that regulatory approached are needed [48], such as increases in the price of SSBs through taxation [13, 49]. Although there is some evidence to suggest that in principle, an SSB tax could reduce consumption [50], further evidence is needed based on observed rather than modelled effects [51]. Preliminary results of the effects of an SSB tax in Mexico (constituting approximately a 10 % increase in price per litre) shows a 10 % decline in purchases in the first quarter of 2014 compared to the first quarter of 2013 [52]. The policy awaits further evaluation. Discussions regarding implementation of taxes on SSBs in other countries have been met with objections, such that it would unfairly penalise low-income individuals and households and would unfairly single out one type of food [51]. This highlights the need to also explore further, potentially more acceptable ways of reducing SSB consumption. Another potentially effective regulatory approach [34] that might be more acceptable than taxation is to restrict serving sizes. However, the impact of such an intervention has yet to be thoroughly examined. Simulation studies suggest that the introduction of a restriction on available beverage sizes, such as the ban proposed by the mayor of New York City on sales of SSBs larger than 16 oz (473 ml), could have favourable effects on consumption [53, 54]. However, there is currently a lack of experimental evidence—as opposed to evidence from simulation studies—to support the use of such an intervention. In addition, the impact of presenting the same total amount of a beverage in multiple, smaller packages on SSB consumption is unknown.

The current feasibility and acceptability study is designed to finalise the design and conduct of a future, full-scale trial to assess whether reducing the size of the bottles in which SSBs are presented can reduce consumption. Its primary purpose is to address key design uncertainties for the trial, including the feasibility of recruiting eligible households, the practicalities of delivering the intervention to households and replacing existing SSBs and the feasibility of assessing consumption, as well as the specific bottle sizes that should be targeted. It will be the first study to our knowledge to explore the use a package-size intervention for reducing SSB consumption. Its robust experimental design and naturalistic setting are expected to enhance the value of the findings, whilst inclusion of a qualitative component will also provide a detailed understanding of the acceptability of the intervention. It should be noted,however, that as this is a feasibility study, findings will require replication in larger and more representative samples.

The success of this feasibility and acceptability study will be judged on a number of criteria, including (i) our target sample size is met by approaching 100 households, (ii) recruited households match the deprivation level of typical SSB consumers in the UK (i.e. 50 % are from areas falling under the fourth and fifth IMD quintile), (iii) the majority of participants are not aware of the study’s scientific aim and (iv) at least 12 households out of 16 complete the first intervention period. Should some of these indicators of success not be met, we will consider changes to the study design and procedures before deciding whether and how to proceed with the trial. Specifically, we will consider additional recruitment methods and perhaps widen the target recruitment areas and/or modify the specified eligibility criteria. Larger than expected attrition rates will be accounted for in the trial sample size calculations. Knowledge of the study’s scientific aim could affect the results. Therefore, if we find that most participants are aware of the study aims, we will consider an alternative cover story.

In conclusion, evidence regarding the effectiveness of sizing interventions for reducing SSB consumption is currently lacking. The proposed study will provide information needed to finalise the design of a future crossover randomised controlled trial assessing the impact of reducing bottle size on in-home consumption of SSBs. This trial will provide the best estimate to date of the potential effect of altering the packaging size of SSBs on consumption and thereby inform policy concerning the use of such interventions to reduce consumption to improve population health and reduce health inequalities.

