### Participants

Participating households will be of any size or composition. We define households as people who live together, who may or may not be related but who share all or most drink and food within the house. This includes households consisting ofSingle membersCouples (married or cohabitating)Families with school age childrenSingle parents with dependent childrenFamilies with extended family members living in the house (e.g. grandparents)

In line with the characteristics of the population of SSB consumers in the UK [29], 50 % of the recruited households will be from areas of high deprivation, as defined by their Index of Multiple Deprivation (IMD)^1^ [32] score, with areas falling under the fourth and fifth IMD quintile considered highly deprived. Inclusion criteria for participating households are as follows:i.Purchase regular (not low sugar) Coca-Cola**®** or Pepsi Cola**®** at a minimum rate of 2 l a week.ii.Reside in or near to Cambridge, UK, within 10 miles of the research team base.iii.Do not plan to be away from home for longer than 7 days during the study period.

We will recruit one individual from each eligible household to act as a household representative, who will consent to participation in the study for the entire household and provide all necessary data. In order to evaluate recruitment rates, we will initially approach 100 eligible households with the aim of assessing how many would be interested in taking part in the study and how many would complete the run-in period (see ‘Procedure’ section for details). We assume that households completing this period would be likely to continue, completing at least one intervention period. Of the households completing the run-in period and expressing a willingness to continue with the study, we will invite 16 to continue their participation and undergo the intervention periods. If fewer than 16 households complete the run-in period, we will approach additional households.

Households will be identified and recruited through a research agency.

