All participating households will receive all interventions according to a pre-specified random order (see ‘Randomisation’ section for details). During the first intervention period, four households will receive cola in each of the intervention bottle sizes, subsequently crossing-over to the other conditions during the remaining three intervention periods, until all households have been exposed to all conditions. All intervention periods will be conducted during school term times, in order to avoid increased consumption during any specific period due to the increased presence of children in the homes. During the intervention periods, a researcher will visit participating households to deliver the total volume of the cola (Coca-Cola**®** or Pepsi Cola**®** depending on their preference) SSB for the forthcoming week. The researcher will remove any existing SSB products that are in the household, with financial compensation provided for any removals. At the end of each week, households will be requested to pay for the SSB drinks they consume at their usual purchasing rate. During the intervention periods, households will be requested to continue to keep all bottles whether the contents are consumed, partially consumed or not consumed. They will be told that the reason for this is to accurately estimate how much they need to pay for their drinks, based on the amount they consumed.

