### Randomisation

Randomisation will be restricted to ensure that (a) equal numbers of households receive each of the four bottles sizes at each intervention period (Table 1) and (b) each bottle size is equally likely to be preceded and followed by each other bottle size. These conditions are imposed to ensure that the order in which the interventions are presented is counterbalanced and that outcomes are not affected by potential order and carry-over effects. In a larger trial, such as the future one we are planning, we do not foresee the need for imposing such restrictions, as randomisation of a large number of households is expected to minimise the chance of imbalances in the order of the interventions.

**Table 1 Tab1:** Number of households allocated to each bottle size during each intervention period

	Bottle size			
	250 ml	500 ml	1000 ml	1500 ml
Intervention period 1	*n* = 4	*n* = 4	*n* = 4	*n* = 4
Intervention period 2	*n* = 4	*n* = 4	*n* = 4	*n* = 4
Intervention period 3	*n* = 4	*n* = 4	*n* = 4	*n* = 4
Intervention period 4	*n* = 4	*n* = 4	*n* = 4	*n* = 4

We will initially randomly select four sequences (out of 24 available sequences) dictating the order in which households receive each bottle size. These four sequences will then be used to determine the other 12 sequences needed to balance the initial allocations to ensure that the aforementioned conditions are met. Each household will be randomly allocated to one of these 16 sequences. In this manner, the order in which each household receives each bottle size will be pre-specified at the start of the study. The randomisations will be determined during the run-in period (see ‘Procedure’ section) by a statistician independent from the research team, with the assistance of computer software.

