### Procedure

Participation will comprise seven stages:Two-week recruitment and baseline assessment period (see ‘Baseline assessments’ section for details).One-week run-in period. Households will receive a range of differently sized bottled drinks to store in their homes to consume freely. This period functions to acquaint them with both the idea that a wide range of bottle sizes is available and that drinks will be delivered to them over the course of the study. More generally, it will build credibility of the study as a consumer research exercise. Study randomisation will be conducted during this period.First intervention period: 1 week in duration.Second intervention period: 1 week in duration.Third intervention period: 1 week in duration.Fourth intervention period: 1 week in duration.End of study and debriefing.

Stages 1–2 will be completed by any number of eligible households out of the 100 approached that agree to do so.

Stages 3–7 will be completed by 16 households, randomly selected from those completing stages 1–2, who also express a willingness to continue participation in the study. If only 16 households agree to continue their participation, all will be invited to complete these additional stages.

Each household will receive £150 worth of shopping vouchers at the end of the study for completion of all intervention periods and follow-up assessments. This amount was determined based on the national minimum wage rates per hour and the level of commitment and amount of time spent participating in the study (approximately 25 h during 5-week period). Households completing the run-in period but not invited to continue their participation, or not interested in continuing, will receive £30 worth of shopping vouchers.

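### The only named retention indicator stops at week 1 of a four-week crossover, so it can be met without any household receiving a second bottle size

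*Protocol article*

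**What the plan says.** The Discussion introduces its list with "The success of this feasibility and acceptability study will be judged on a number of criteria, including" and then names four items: recruitment, deprivation mix, unawareness of the aim, and retention. The retention item is that "at least 12 households out of 16 complete the first intervention period". The Participants section applies the same one-period standard to households that finish the run-in: "We assume that households completing this period would be likely to continue, completing at least one intervention period".

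The design sections ask for more. Under Intervention, "All participating households will receive all interventions according to a pre-specified random order", with crossing over to continue "until all households have been exposed to all conditions". Under Procedure, "Stages 3–7 will be completed by 16 households", and those stages include all four intervention weeks. Under Randomisation, "Each household will be randomly allocated to one of these 16 sequences", and the sequences are chosen so that "each bottle size is equally likely to be preceded and followed by each other bottle size". The Design section justifies the crossover by the control it gives over differences between households.

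Later loss is not ignored. Loss to follow-up is an objective, households discontinuing at follow-ups is a feasibility outcome, a follow-up takes place at the end of each intervention week, and attrition rates are part of the main analysis. The Discussion adds that attrition above expectation will be allowed for in the main trial's sample size. No section states the expected rate or sets a threshold for completing weeks 2 to 4.

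**The concern.** The benchmark does not match the design it is meant to judge. The advantage of a crossover comes from observing the same household under two or more bottle sizes. Criterion (iv) asks only whether households finish one size, which shows uptake after the run-in. It does not show whether households will put up with repeated deliveries, removal of existing drinks, bottle retention and measurement over successive weeks.

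At stake is how informative the feasibility verdict is. The retention indicator could be reported as met when few households had completed the sequence, and the article offers no other stated yardstick against which loss in weeks 2 to 4 would count as a problem.

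**Working it through.** **Inputs from the article.** 16 households; 4 one-week periods; Table 1 with 4 households per size per period; 16 sequences; threshold 12 of 16 in period 1. The article derives no power, dropout or retention figure, so the only figure of its own to reproduce is the threshold: 12/16 = 75%.

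**Least information compatible with meeting the indicator.**
- Planned household-weeks: 16 × 4 = 64, which agrees with Table 1 (16 cells of 4).
- Household-weeks needed to meet (iv): 12, that is 12/64 = 19%.
- Planned moves from one size to the next: 16 × 3 = 48. There are 4 × 3 = 12 ordered pairs of sizes, so the balance condition implies 48/12 = 4 moves per pair. The number of moves needed to meet (iv) is 0.

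**Illustration over a range of retention.** The article gives no weekly retention rate, so r is an assumption: constant from week to week, with households independent. The number completing week 1 is then binomial(16, r), and the number completing all four weeks is binomial(16, r⁴). Anyone who completes four weeks has completed week 1. The chance that (iv) is met while fewer than 12 complete the sequence is therefore the difference between the two tail probabilities.

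| r | P(at least 12 complete week 1) | Expected to complete all four, 16r⁴ | P(at least 12 complete all four) | P(week-1 rule met, fewer than 12 complete all four) |
|---|---|---|---|---|
| 0.95 | 0.999 | 13.0 | 0.840 | 0.16 |
| 0.90 | 0.983 | 10.5 | 0.307 | 0.68 |
| 0.85 | 0.921 | 8.4 | 0.055 | 0.87 |
| 0.80 | 0.798 | 6.6 | 0.006 | 0.79 |
| 0.75 | 0.630 | 5.1 | <0.001 | 0.63 |

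To expect 12 of 16 at the end of week 4, weekly retention must be 0.75^(1/4) = 0.93.

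**Starting from a bare pass.** If exactly 12 finish week 1 and retention is 0.90 a week after that, 12 × 0.9³ = 8.7 households are expected to complete the sequence.

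**Partial completers.** At r = 0.90, 16 × 0.9² = 13.0 households are expected to complete at least two weeks, against 10.5 completing all four. Those with two or three weeks still supply some within-household comparison, so the four-week count understates the usable information.

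**The case against.** The case for leaving the text alone has several sound parts.

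- **The list is soft.** It is open-ended, its items are described as indicators, and missing one leads the team to consider changes before deciding whether and how to go on. A reader might infer a binding go/no-go rule on retention, but the article does not say that meeting (iv) sends the trial ahead or settles that retention is adequate. This stands.
- **Later loss will be seen.** Discontinuation is recorded at each weekly follow-up and attrition is reported. This stands, and it means the remedy needs little new data. But recording a loss is not the same as having a stated benchmark for judging it.
- **The main trial's sample size is not tied to 12/16.** A reader might infer that the main trial would be inflated by 1/0.75 = 1.33 when 1/0.75⁴ = 3.16 was needed. The documents do not support this. Nothing feeds the week-1 figure into that calculation, and the statement on allowing for attrition is not limited to week 1. The larger factor also assumes a quarter lost every week and gives no value to households with two or three weeks.
- **Retention may be good.** Households entering week 1 have finished a run-in and said they are willing to continue, and the £150 voucher is for completing all intervention periods and follow-up assessments. This is a fair reason to think that the low end of the range is pessimistic.
- **A week-1 household is not worthless.** The stated analysis is change from baseline in each period, and such a household contributes to that. It contributes nothing to a comparison between sizes, which is the purpose of the crossover.
- **Criterion (iv) may be meant as an uptake check** on the assumption in the Participants section. That is a reasonable reading, but it would leave the list with no indicator of retention through the crossover.

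**Conclusion.** The point holds as a mismatch between a stated indicator and the stated design. Criterion (iv) is the only named retention indicator, and it can be met with 12 of 64 household-weeks and no household receiving a second size. That much follows from the article alone. The probabilities rest on an assumed constant weekly retention and independent households. At 0.90 the indicator is met about 98% of the time, with about 10.5 of 16 expected to finish the sequence. At 0.95 the gap is small, and at 0.85 it is wide.

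The weight is modest. The article contains no binding decision rule and no under-inflated main-trial sample size, and it already collects the data that would expose late attrition. This is a worthwhile, inexpensive correction and not an error that invalidates the study.

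**What to change.** Rewrite criterion (iv) so that it counts households completing all four intervention periods with measured consumption in each. The sponsor should choose and justify the threshold. Carrying 12 of 16 over unchanged is a choice that needs a reason, because at 0.90 weekly retention it would be met only about 31% of the time.

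Alongside it:
- keep week-1 completion as a descriptive uptake figure;
- report retention by week, and the number of households giving consent to data use after the debrief;
- state the attrition rate that the phrase on larger-than-expected attrition refers to;
- base the main trial's attrition allowance on observed loss across all periods, giving credit to households that complete some but not all of them.

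The change to the criterion is one sentence, and the reporting items add a few lines. Discontinuation, weekly consumption and post-debrief consent are already to be collected. The downside is a stricter hurdle that is more likely to be missed, which under the Discussion's own terms would lead the team to consider changes and would not stop the trial automatically.
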